#### **2.1.2 Secondary objectives**

In patients aged 55 or older, with confirmed or suspected gynecologic cancer, undergoing cytoreductive or high-risk surgery with or without chemotherapy:

1. to compare the predictive performance of *different preoperative/perioperative frailty assessments* for all-cause death or new disability at 6 months after surgery; the different assessments will include:
  - a. different frailty tools, i.e., the whole FP, the single components of the FP, and the CFS;
  - b. a *dynamic* perioperative frailty assessment (i.e., based on a frailty assessment repeated 28 days after surgery, in addition to a preoperative frailty assessment)
  - c. a frailty assessment combining the FP with a cognitive assessment (i.e., *cognitive frailty*)
2. to compare different frailty assessments upon *feasibility* and *acceptance* to patients and healthcare providers;
3. to explore the predictive performance of frailty assessments upon *chemotherapy-related outcomes*, including completion, satisfaction/regret, impact on function, high-grade adverse events and total dose received;
4. to explore the predictive performance of preoperative frailty versus a preoperative cardiovascular risk assessment+age with postoperative trajectories of disability up to 1 year after surgery;
5. to explore the predictive performance of a preoperative frailty assessment and of a preoperative cardiovascular risk assessment based on RCRI+age upon *postoperative outcomes at 28 days after surgery*, including all-cause death or new disability; major vascular events; infection and sepsis; length of stay; unplanned admission to intensive care unit; and delirium.
6. to explore the predictive performance of a perioperative frailty assessment and of a perioperative cardiovascular risk assessment based on RCRI+age combined with MINS, upon other *long-term postoperative outcomes*, including major vascular events at 6 months and 1 year after surgery; infection and sepsis at 6 months and 1 year after surgery; postoperative cognitive dysfunction at 6 months and 1 year after surgery; all-cause death at 6 months and 1 year after surgery; and all-cause death or new disability at 1 year after surgery.
7. to explore the predictive performance of a perioperative frailty assessments and of a perioperative cardiovascular risk assessment based on RCRI+age combined with MINS, upon *oncologic outcomes* of PFS and overall cancer-specific survival (after surgery) up to 1 year after surgery;
8. to explore the value of frailty assessment *when added* to a perioperative cardiovascular risk assessment+age, with or without other clinical predictors, in predicting postoperative outcomes;
9. to create a biobank to explore possible *biomarkers* of perioperative frailty.

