### 3.1.5 Preoperative RCRI+age, combined with MINS

For the purpose of the study, and to reflect the current practice, MINS will be defined as any elevated troponin (higher than the local lab threshold) judged to be due to myocardial ischemia (i.e. without evidence of a non-ischemic etiology [e.g. chronic elevation, pulmonary embolism {PE}, sepsis, cardioversion]) that occurred within the first 28 days after the initiation of surgery. *The only exceptions to the definition of an elevated troponin will be to use a higher threshold for troponin T (TnT) of  $\geq 30$  ng/L, and for high-sensitivity troponin T (hsTnT) of 20 to  $< 65$  ng/L with an absolute change of at least 5 ng/L or an hsTnT level  $\geq 65$  ng/L. These threshold for TnT and hsTnT are based upon data from a large international prospective perioperative cohort study that established troponin thresholds that were independently associated with 30-day mortality after noncardiac surgery.* The occurrence of MINS according to this definition, as a predictor/exposure, will be based on the in-hospital postoperative troponin measurement, and on any other troponin measurement occurring within the 28 days after surgery. For the primary research question, patients will be considered as meeting the MINS definition regardless of whether this meets the universal definition of myocardial infarction.

For the purpose of the primary research questions, study participants will be assigned to the high-risk category (i.e., ‘exposed’) when they are at high risk as per the preoperative RCRI+age assessment

and they experience MINS; and to the low-risk category (i.e., not ‘exposed’), if they are at high risk as per the preoperative RCRI+age assessment but they do not experience MINS, or if they are at low risk as per the preoperative RCRI+age assessment.

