## **6. STATISTICAL ANALYSES**

### **6.1 Primary Analysis**

The primary analysis will compare the performance of preoperative frailty assessment based on the FP and perioperative cardiovascular risk assessment based on the combination of preoperative RCRI, age and occurrence of MINS, in predicting the composite of all-cause death or new disability at 6 months after surgery. We will assess the association of FP and of RCRI+age+MINS with the primary outcome using logistic regression models. We will perform one logistic regression model including frailty as predictor, and one logistic regression model including the baseline RCRI+age+MINS as predictors. For each model we will then calculate the c-statistics (corresponding to the AUROC) and compare them using a non-parametric approach. We will include in the primary analysis only study participants who are alive at 28 days after surgery. We expect this will exclude from the primary analysis a very small proportion of patients initially enrolled in the study (i.e.,  $\leq 2\%$ ). We will initially exclude from the primary analysis those patients for whom postoperative troponin measurement was

not performed (for reasons other than death); as a sensitivity analysis, these patients will be then included and considered as not having MINS. For the primary analysis we will not include other covariates in the regression models. We will secondarily include the type of gynecological diagnosis/indication (based on our inclusion criteria) as covariate and as effect modifier.

As part of our secondary objectives, we will also evaluate the utility of frailty *when added* to the RCRI+age+MINS as predictors by calculating the net absolute reclassification improvement.

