### **Major vascular complications (at 28 days, 6 months, and 1 year after surgery)**

It is defined as a composite of vascular death, and non-fatal myocardial infarction (or myocardial injury for the 28-day time point), stroke, symptomatic proximal venous thromboembolism, and cardiac arrest. The definitions for the components of the composite are the following:

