#### *Myocardial Injury after Noncardiac Surgery (MINS)*

MINS is defined as any myocardial infarction (as defined below), and any elevated troponin (higher than the local lab threshold) judged to be due to myocardial ischemia (i.e. without evidence of a non-ischemic etiology [e.g. chronic elevation, PE, sepsis, cardioversion]) that occurred within the first 28 days after the initiation of surgery. The only exceptions to the definition of an elevated troponin will be to use a higher threshold for TnT of  $\geq 30$  ng/L, and for hsTnT of 20 to  $< 65$  ng/L with an absolute change of at least 5 ng/L or an hsTnT level  $\geq 65$  ng/L. These thresholds for TnT and hsTnT are based upon data from a large international prospective perioperative cohort study that established troponin thresholds that were independently associated with 30-day mortality after noncardiac surgery.

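### Objective 6 counts a perioperative MI both as predictor (through MINS to day 28) and as outcome (6-month and 1-year vascular composite), which favours the cardiovascular model over frailty

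*Protocol*

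**What the plan says.** Protocol 2.1.2, objective 6, sets a perioperative frailty assessment beside "a perioperative cardiovascular risk assessment based on RCRI+age combined with MINS, upon other" long-term outcomes, "including major vascular events at 6 months and 1 year after surgery; infection and sepsis at 6 months and 1 year after surgery". Objective 7 uses the same predictors for PFS and cancer-specific survival.

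Section 3.1.5 takes MINS as an ischaemic troponin elevation "that occurred within the first 28 days after the initiation of surgery", based on the in-hospital measurements "and on any other troponin measurement occurring within the 28 days after surgery". It adds, expressly for the primary research question, that MINS counts "regardless of whether this meets the universal definition of myocardial infarction". Appendix II carries the inclusion of MI into the general definition: "MINS is defined as any myocardial infarction (as defined below), and any elevated troponin". It also requires any troponin-based MI to meet the MINS definition.

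For the vascular outcome, Appendix II says: "It is defined as a composite of vascular death, and non-fatal myocardial infarction". The parenthesis that follows admits myocardial injury as an alternative to MI at the 28-day time point only. Stroke, symptomatic proximal VTE and cardiac arrest complete the composite. Section 4.2 lists it at 28 days, 6 months and 1 year after surgery.

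The only landmark is in section 6.1: "We will include in the primary analysis only study participants who are alive at 28 days after surgery". Section 6.2 names logistic or time-to-event models for the other outcomes and gives no landmark.

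**The concern.** A prediction analysis needs a predictor that is settled before the outcome begins to accrue. Here the predictor window (surgery to day 28) lies inside the outcome window (surgery to 6 months or 1 year), and one event, MI, belongs to both. Part of the apparent performance of RCRI+age+MINS for major vascular events is then true by definition. Preoperative frailty gets no such credit, so the comparison is tilted towards the cardiovascular assessment.

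The protocol avoids this under objective 5, where the 28-day outcomes are predicted from RCRI+age without MINS. Objective 6 has no matching safeguard, although its cumulative outcomes contain the same 28 days.

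**Working it through.** **Windows and definitions side by side**

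- Predictor: MINS, day 0 to day 28, including any MI (3.1.5; Appendix II, MINS).
- Outcome: non-fatal MI and vascular death at 6 months and 1 year after surgery, with no later start (4.2; Appendix II, Major vascular complications).
- Shared events: MI in days 0 to 28, and vascular death that follows such an MI.
- Not shared at 6 months and 1 year: myocardial injury without MI, which enters the composite only at 28 days.
- VTE and sepsis: no shared event. A troponin rise attributed to PE or sepsis is excluded from MINS, so an early PE or sepsis can affect MINS classification in the opposite direction.
- Death, PFS and cancer-specific death: no shared event beyond MI-related death. Early events may precede a predictor that stays open until day 28. For PFS, Appendix II uses frailty measured before surgery (or before the first treatment), so there the timing issue concerns MINS only.

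**Size**

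The protocol states no MINS or MI rate, so there is no figure to reproduce and all inputs are assumptions: MINS p = 15%, MI within 28 days m = 3% (all MINS-positive), other vascular events o = 5% unrelated to MINS. MINS is taken alone as a yes/no predictor, for which AUC = 0.5 + (sensitivity − false-positive rate)/2.

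(a) Other events are 5% of all patients, added to the MIs, with 15% of them falling in MINS-positive patients:

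- sensitivity = (0.03 + 0.05 × 0.15)/(0.03 + 0.05) = 0.0375/0.08 = 0.469
- false-positive rate = (0.15 − 0.0375)/0.92 = 0.122
- AUC = 0.5 + (0.469 − 0.122)/2 = 0.673

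(b) Other events are a 5% risk among patients without an early MI:

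- all events = 0.03 + 0.05 × 0.97 = 0.0785
- events in MINS-positive patients = 0.03 + 0.05 × 0.12 = 0.036
- sensitivity = 0.036/0.0785 = 0.4586
- false-positive rate = (0.15 − 0.036)/0.9215 = 0.1237
- AUC = 0.5 + (0.4586 − 0.1237)/2 = 0.667

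Counting only events after day 28, at the same 5% risk with or without MINS, sensitivity and false-positive rate are both 0.15 and the AUC is 0.50.

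Range over m = 2–4%, p = 12–15%, o = 4–6%:

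- lowest (m 2%, p 15%, o 6%): 0.62 under (a), 0.61 under (b)
- highest (m 4%, p 12%, o 4%): 0.74 under (a), 0.73 under (b)

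Wider assumptions (MINS 5–20%, MI in 20–50% of MINS, later risk 5–10%) give 0.54 to 0.81. In the middle case (15%, 30%, 10%), 280 × 0.15 × 0.30 = 12.6 patients carry the same MI on both sides. They are 0.045/0.1405 = 32% of composite events, and the AUC is 0.64.

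**The case against.** The other side has several fair points.

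- The composite already drops myocardial injury without MI after day 28. This stands, and it confines the identity to MI and MI-related vascular death. A reader might infer that the whole frailty-versus-cardiovascular comparison, including sepsis, VTE, death and PFS, is partly true by definition. The definitions do not support that: those outcomes raise time order and the exclusion of some troponin rises, and no size can be put on either from the protocol.
- The sentence in 3.1.5 keeping MI within MINS is limited to the primary question. True, but the Appendix II definition includes MI without that limit.
- Accrual from surgery is inferred. The protocol never spells out the event window, and an analysis plan not available here could restrict it. It remains the natural reading of outcomes at 6 months and 1 year after surgery, and no other is written. The overlap itself comes from definitions that the protocol fixes.
- MINS is not unknown until day 28 in everyone. Section 5.1 schedules troponins through the third postoperative day or discharge; later values are incidental. The definition nevertheless stays open to day 28.
- The exclusion for PE and sepsis removes a troponin rise with that cause, not the patient. This stands.
- Objective 1b might look unprotected too. It concerns the primary outcome, and a 28-day change in frailty already requires survival to that visit.
- The illustration uses MINS alone, and the combined classification could dilute it. If every participant scores the RCRI point for high-risk surgery, the category in 3.1.5 reduces to MINS and there is little dilution; the protocol does not say whether all will.

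**Conclusion.** The point holds for the major vascular composite at 6 months and 1 year. Following the protocol as written counts the same perioperative MI as predictor and outcome, and the bias runs in favour of the cardiovascular model. On assumed rates, a MINS indicator with no value for later events would show an AUC of about 0.67, and roughly 0.61 to 0.74 over the narrower range. These figures illustrate the mechanism and do not forecast the result.

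For VTE, sepsis, death, PFS and cancer-specific death the problem is one of time order, real but lesser and not quantified.

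A reader might infer that the primary comparison is contaminated as well. It is not: its outcome is death or new disability, MI is not a component, new disability is measured at the 6-month visit, and section 6.1 restricts the analysis to patients alive at day 28. The sample size is likewise untouched. Objectives 6 and 7 are exploratory, so this is a correction worth making but no threat to the main conclusion.

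**What to change.** Add a paragraph to section 6.2. For event outcomes under objectives 6 and 7, and under objective 8 when MINS is in the model, any analysis using MINS or the 28-day frailty score includes patients alive at day 28 and counts only events after day 28. For PFS, patients must also be progression-free at day 28. Models being compared should use the same patients and events.

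Requiring survival to day 28 is not enough alone, because an earlier non-fatal MI would still count as an outcome. Patients with such an MI stay in the analysis; only the early event is not counted. Outcomes measured at the 6-month and 1-year visits (disability, MoCA) need no change to the event window.

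The cost is fewer events in exploratory models. Early vascular events, infection or sepsis, and deaths remain under objective 5, which uses preoperative predictors. Early progression and cancer-specific death are not listed there, so they should be reported separately or analysed from surgery with preoperative predictors only (FP, RCRI+age).

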## 2.2 Study Design

This is a multicentre prospective cohort study of patients 55 years old or older with confirmed or suspected gynecologic cancer who are candidates to cytoreductive or high-risk surgery (laparotomy) with or without chemotherapy at centres.

## 2.3 Sample Size

The FARGO study is sized to respond to the primary objective. We expect a 20% rate of death or new disability at 6 months after surgery (primary outcome). We performed preliminary analyses of the VISION cohort, where data for women undergoing surgery for gynecologic cancer could not be distinguished from women undergoing surgery for urological cancer. Based on these analyses, we expect that, in our study population, the ability of the baseline RCRI+age combined with the occurrence of MINS to predict 6-month death or new disability, measured as Area Under the receiver operating characteristic Curve (AUC), will not be greater than 0.600 (range 0.550-0.600, Appendix I).

A sample size of 280 patients will give us at least 80% of power to detect a difference of at least 0.130 in the AUC for a model including only the FP-frailty assessment, compared with the AUC for the model including preoperative RCRI+age combined with MINS (i.e., AUC for FP-frailty model of at least 0.680^21). The table in the Appendix I shows the sample size calculation based on these assumptions for a range of scenarios, based on the comparison of 2 Receiving Operating Characteristic (ROC) curves, 2-sided test, alpha=0.05, and assumed correlation between the 2 predictive models=0.5.

We will include 280 patients in order to conservatively account for  $\leq 10\%$  of participants who will be lost before or during surgery, and in whom troponin measurement to assess for MINS will not be possible (in fact, we expect that after recruitment much fewer patients will not undergo or survive surgery). Based on our eligibility criteria, we expect that at least 50% (i.e., 140) of our participants will undergo chemotherapy, before and or after surgery, and will be included in our exploratory secondary analyses on chemotherapy outcomes.

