(ECG) changes, is associated with a >3 fold increase in any-cause mortality within 30 day from surgery, with the highest attributable risk for death (34%) among all major postoperative complications. MINS is also strongly associated with mortality at 1 year. Embedding this evidence, the Canadian guidelines recommend a preoperative cardiovascular risk stratification that starts with calculating the RCRI; in those with a RCRI  $\geq 1$ , or with a RCRI=0 but 65 years old or older, troponin monitoring for the first 3 days after surgery is recommended.

These perioperative risk guidelines are followed in many centres in Canada and worldwide. However, this approach might have limitations in the GO population. Unpublished confidential data from VISION show that, among 271 women aged 55 or older undergoing major surgery for uro-gynecologic cancers, MINS was associated with a 2-to-3-fold increase in mortality at 1 year; however, those with no MINS (and not meeting the RCRI+age criteria for high risk) still had a 1-year mortality of 14% (compared to 3% in same age women in the overall VISION cohort without MINS). Limitations of the VISION study in order to inform our current practice with GO patients include: poor representation of this population; no collection of data on cancer-specific risk factors, and on preoperative and postoperative chemotherapy; no predictive ability for non-cardiac postoperative morbidity, and no intermediate time points (i.e. >30 days and <1 year). In addition, VISION did not include the assessment of patient reported outcomes (PROs), like QoL, functional recovery, or disability, which are poorly studied in the GO literature, but might be the most relevant to patients.

At no time does the current perioperative assessment of GO patients include frailty.

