# Appendices

## Appendix I. Sample size calculations

The sample size calculation is based on the comparison of two receiver operator characteristic curves (ROC), 2-sided test, with alpha=0.05. The assumed AUC for the RCRI, age, and MINS model is 0.55 (AUC1). The assumed AUC of the frailty assessment model is between 0.65-0.75 (AUC2). The assumed AUC difference is approximately 0.13. We expect an incidence of the primary outcome (all-cause death or disability at 6 months after surgery) to be 20%.

A sample size of 250 patients will give us at least 80% of power to detect a difference of at least 0.130 in the AUC for a model including only the FP-frailty assessment, compared with the AUC for the model including preoperative RCRI and age combined with MINS.

The assumed correlation between the two predictive models is 0.50 for the positive group (those experiencing the outcome) and 0.50 for the negative group (those not experiencing the outcome)

We will include 280 patients to conservatively account for ≤10% who will be lost before or during surgery, or in whom biomarker measurement will not be possible.

Software: PASS 13 (NCSS, LLC. Kaysville, Utah, USA. [www.ncss.com](http://www.ncss.com))

Sample size calculation

| AUC1 | AUC difference | AUC2 | Target power | Sample size |
|------|----------------|------|--------------|-------------|
| 0.55 | 0.10           | 0.65 | 80%          | 405         |
| 0.55 | 0.10           | 0.65 | 85%          | 465         |
| 0.55 | 0.10           | 0.65 | 90%          | 545         |
| 0.55 | 0.13           | 0.68 | 80%          | 240         |
| 0.55 | 0.13           | 0.68 | 85%          | 280         |
| 0.55 | 0.13           | 0.68 | 90%          | 325         |
| 0.55 | 0.15           | 0.70 | 80%          | 185         |
| 0.55 | 0.15           | 0.70 | 85%          | 210         |
| 0.55 | 0.15           | 0.70 | 90%          | 245         |
| 0.60 | 0.10           | 0.70 | 80%          | 425         |
| 0.60 | 0.10           | 0.70 | 85%          | 485         |
| 0.60 | 0.10           | 0.70 | 90%          | 570         |
| 0.60 | 0.13           | 0.73 | 80%          | 250         |
| 0.60 | 0.13           | 0.73 | 85%          | 290         |
| 0.60 | 0.13           | 0.73 | 90%          | 340         |
| 0.60 | 0.15           | 0.75 | 80%          | 190         |
| 0.60 | 0.15           | 0.75 | 85%          | 220         |
| 0.60 | 0.15           | 0.75 | 90%          | 255         |

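### Section 2.3 equates a 0.130 AUC gain with a frailty AUC of at least 0.680, which is true only at a comparator AUC of 0.55; at the plan's 0.60 ceiling, power at 0.68 is about 42%

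*Protocol*

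**What the plan says.** Protocol section 2.3 (Sample Size) expects the model with RCRI, age and MINS to have an AUC that "will not be greater than 0.600 (range 0.550-0.600, Appendix I"). It then says that 280 patients give "at least 80% of power to detect a difference of at least 0.130 in the AUC", and adds in parentheses that this means "AUC for FP-frailty model of at least 0.680", with a literature citation attached to that value. The test settings are "2-sided test, alpha=0.05, and assumed correlation between the 2 predictive models=0.5".

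Appendix I attaches the same claim to the analysable number: "A sample size of 250 patients will give us at least 80% of power to detect a difference of at least 0.130". Its text fixes the comparator AUC at 0.55, but its table runs over both 0.55 and 0.60. At 80% power the table prints 240 patients for 0.55 v 0.68 and 250 for 0.60 v 0.73. It pairs 0.68 with 0.55 only and has no row for 0.60 v 0.68.

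The step from 250 to 280 is an allowance of up to 10%, described in section 2.3 as being for those "of participants who will be lost before or during surgery, and in whom troponin measurement to assess for MINS will not be possible". Section 6.1 separately excludes from the primary analysis patients who are not alive at 28 days, expected to be at most 2%.

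**The concern.** The parenthesis turns a statement about a difference into a statement about a level. The two agree only if the comparator sits at the bottom of the range given two sentences earlier: 0.550 + 0.130 = 0.680, but 0.600 + 0.130 = 0.730.

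Because 0.680 carries a citation, it reads as the performance expected of the Frailty Phenotype, and 0.600 is the protocol's own ceiling for the comparator. A study that met both expectations would be looking for a difference of 0.08, which the sample size was not built to detect. Someone relying on section 2.3 would believe that a frailty AUC of 0.68 is covered at 80% power wherever the comparator falls in its range, and could give a non-significant comparison more weight than it deserves.

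**Working it through.** **Inputs, all from section 2.3 and Appendix I.** Two-sided alpha 0.05; outcome rate 20%, so R = 4 non-events per event; correlation 0.5 ("The assumed correlation between the two predictive models is 0.50 for the positive group", and the same for the negative group); comparator AUC 0.55 to 0.60; frailty AUC 0.68; 250 analysable, 280 enrolled, and 280 × 0.90 = 252.

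**Formula.** Binormal variance and covariance for two correlated AUCs (Obuchowski–McClish), per event, with A = √2·Φ⁻¹(AUC) and r = 0.5:

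- V(A) = e^(−A²/2)/(32π) × [(5A² + 8) + (A² + 8)/R]
- C(A₁,A₂) = e^(−(A₁²+A₂²)/4) × {[r + r/R + r²A₁A₂/2]/(4π) + [A₁A₂(r² + R·r²)/(2R)]/(16π) − A₁A₂r²/(8π)}
- v₁ = V(A₁) + V(A₂) − 2C(A₁,A₂); v₀ is the same with both AUCs set to the comparator value
- N = 5 × (1.960√v₀ + z_power√v₁)² / (AUC₂ − AUC₁)²
- Power = Φ{[(AUC₂ − AUC₁)√(N/5) − 1.960√v₀] / √v₁}

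**Reproducing the plan, 80% power (z = 0.8416).**

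- 0.55 v 0.68: v₀ = 0.10097, v₁ = 0.10871; N = 5 × (0.6228 + 0.2775)² / 0.0169 = 239.8. Stated: 240.
- 0.60 v 0.73: v₀ = 0.10511, v₁ = 0.11346; N = 5 × (0.6354 + 0.2835)² / 0.0169 = 249.8. Stated: 250.

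All 18 rows of the Appendix I table come back when the computed N is rounded up to the next multiple of 5, so this is in effect the plan's own calculation.

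**The claim about a 0.130 difference.** Power for 0.55 v 0.68 is 81.6% at 250 and 81.9% at 252. For 0.60 v 0.73 it is 80.0% and 80.3%. The claim holds at both ends of the range.

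**Frailty AUC 0.68 against comparator 0.60.** v₀ = 0.10511, v₁ = 0.11023, difference 0.08.

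- N for 80% power = 5 × (0.6354 + 0.2794)² / 0.0064 ≈ 654
- Power at 252: √(252/5) = 7.099; (0.5679 − 0.6354)/0.3320 = −0.203; Φ = 0.419
- Power at 280: √(280/5) = 7.483; (0.5987 − 0.6354)/0.3320 = −0.111; Φ = 0.456

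**Across the comparator range, frailty AUC held at 0.68:**

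| Comparator AUC | Power, N = 250 | N = 252 | N = 280 |
|---|---|---|---|
| 0.55 | 81.6% | 81.9% | 85.6% |
| 0.56 | 75.1% | 75.4% | 79.6% |
| 0.57 | 67.6% | 67.9% | 72.4% |
| 0.58 | 59.3% | 59.6% | 64.0% |
| 0.59 | 50.5% | 50.8% | 54.9% |
| 0.60 | 41.7% | 41.9% | 45.6% |

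Power crosses 80% at a comparator of about 0.553 for 250 to 252 patients and about 0.559 for 280.

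**Cross-check from the plan's own table.** The row 0.60 v 0.70 needs 425 for 80% power. Scaling by the squared difference, 425 × (0.10/0.08)² = 664, and the same scaling gives about 41% power at 252. A Hanley–McNeil variance gives 41 to 42% at 252, and using the alternative variance throughout gives 40%.

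**Secondary: the evaluable number.** As worded, the 10% allowance covers neither the 28-day exclusion nor a missing 6-month WHODAS, without which a survivor has no primary outcome. The protocol gives no rate for the latter, so 5 to 10% is assumed here. Taking every loss in full:

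- 280 × 0.90 × 0.98 × 0.95 = 234.6, or 235
- 280 × 0.90 × 0.98 × 0.90 = 222.3, or 222

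| Scenario | N = 235 | N = 222 |
|---|---|---|
| 0.55 v 0.68 | 79% | 77% |
| 0.60 v 0.73 | 78% | 75% |

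**The case against.** The best defence is that the operative sentence is about a difference of at least 0.130, and that sentence is right. A contrast of 0.60 with 0.68 is a difference of 0.08, below the declared target. The parenthesis could be read as the lowest frailty AUC that would qualify, given the 0.55 assumed in the Appendix I text. The table also prints 0.60 v 0.73 and shows that a difference of 0.10 already needs 405 or 425 patients. Most of this stands: a reader might infer that the power statement as a whole is false or that the trial is too small for its stated target, and the documents do not support either. What remains is that section 2.3 offers 0.680 as the meaning of 0.130 immediately after allowing a comparator of up to 0.600.

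A reader might also infer that the comparator range is misattributed, because section 1.2.2 says the VISION cohort did not assess disability and had "no intermediate time points (i.e. >30 days and <1 year"). That goes too far. Section 2.3 words the range as an expectation for the study population, and Appendix I calls the AUC assumed. The preliminary analyses are not shown, so what they supplied cannot be judged.

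On the evaluable number, the 5 to 10% is not in the protocol, deaths after day 28 are events that need no WHODAS, follow-up may be by telephone, and section 2.3 expects surgical losses well under 10%. With 5% early loss (also an assumption), 280 × 0.95 × 0.98 × 0.95 is about 248, close to what the table requires. That part is therefore secondary.

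**Conclusion.** The point holds for the 0.680 equivalence and not for the 0.130 claim. Taken as a level, 0.680 has 80% power over only the first 0.003 of the 0.05-wide comparator range with 250 to 252 analysable patients, or the first 0.009 if all 280 are analysable. At the ceiling of 0.60, power is about 42% with 252 analysable and about 46% with 280. These figures rest on the plan's own 20% outcome rate, 0.5 correlation and two-sided 0.05 test, and on a method that reproduces its table; other variance formulas move the 42% by a point or two. The attrition effect is small, at most about five percentage points below 80%, and depends on assumed missingness. It justifies stating the evaluable number, not a claim that the enrolment target is wrong.

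**What to change.** Leave enrolment at 280 and change the text:

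1. In section 2.3, replace the single value 0.680 with the frailty AUC detectable with 80% power: 0.68 to 0.73 as the comparator goes from 0.55 to 0.60.
2. Disclose, in section 2.3 or as a row in Appendix I, that 0.60 v 0.68 has about 42% power at 252 analysable patients (about 46% at 280).
3. Align the Appendix I text, which assumes a comparator of 0.55 only, with the 0.550 to 0.600 range used in section 2.3 and in the table.
4. State the evaluable number after all planned exclusions, including death by 28 days and missing 6-month WHODAS, with the assumed missing rate and the resulting power for both scenarios.

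The cost is a few sentences and possibly one table row. Design, endpoint, analysis and conduct are untouched; the stated figures become less favourable.
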